### Outcomes

#### Cognitive Function

The primary outcome of the EFFECT study is the difference in postprandial cognitive score between control and walnut interventions. Additionally, the difference in change of premeal score at the start and end of the intervention period between the control and walnut interventions will be analyzed. To assess cognitive function, the National Institutes of Health Toolbox for the Assessment of Neurological and Behavioral Function Cognitive Battery (NIHTB-CB) was used, specifically the fluid cognition battery. The tests are fully automated and administered via an iPad (Apple Inc) with consistent program-derived instructions. Minimal practice effects and no floor or ceiling effects are seen with the NIHTB-CB [48-50].

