### Sample Size

The primary outcome used in sample size calculation was the postprandial cognitive test score from the NIHTB-CB. Based on our previous study [22], we obtained the SD (11.0) of the difference in postprandial cognitive test score between the unsaturated fat meal and the saturated fat meal. We had 80% power with 78 participants to detect a difference of 3.5 in postprandial cognitive test score between the control and the walnut group using a 2-sided paired *t* test with a type I error of 0.05.

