### Statistical Analysis

Postprandial cognitive test scores will be compared between the control and walnut group using a 2-sided paired *t* test to account for the cross-over design. To further adjust for covariates, a linear mixed effect model with subject-specific random intercept will be fit on postprandial test score with the following covariates: study group, preprandial test score at week 0 and 6, BMI, age, sex, education level, and depression score. The regression coefficient of this study’s group will be the adjusted difference in postprandial test score between this study’s groups. Potential carryover of treatment effects from the first treatment period to the second period will be assessed by including an interaction between treatment and period in the mixed-effect models. Significant interaction indicates the existence of a carryover effect, in which case we will only use data from the first treatment period to evaluate the treatment effect using a 2-sample *t* test and linear regression models. Analyses for the primary hypothesis will use participants who completed the entire study and will be based on an intention-to-treat principle, regardless of compliance and study group crossover. Sensitivity analyses will be conducted with multiple imputation on missing values for participants who do not complete the entire study. A linear mixed effect model with subject-specific random intercept will be fit on preprandial test score at week 1 and 6 with the following covariates: study group, preprandial test score at day 0 and 35, BMI, age, sex, and education level. The regression coefficient of this study’s group will be the adjusted difference in preprandial test score after a 7-day intervention between study groups. A linear mixed effect model with subject-specific random intercept will be fit on postprandial test score at weeks 0 and 5 with the following covariates: change in plasma sum of ALA+LA during 7-day intervention, BMI, age, sex, and education level. The regression coefficient of plasma sum of ALA+LA will measure the adjusted correlation between postprandial test score and change in plasma sum of ALA+LA.

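### Entering the period-specific pretest as one covariate beside a random intercept makes the adjusted walnut effect less precise than it need be, in both cognitive mixed models

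*Protocol article*

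**What the plan says.** The Cognitive Function section fixes the outcome: "The primary outcome of the EFFECT study is the difference in postprandial cognitive score between control and walnut interventions". Sample Size powers a 2-sided paired t test at a type I error of 0.05: "We had 80% power with 78 participants to detect a difference of 3.5 in postprandial cognitive test score". The variability comes from the team's previous study: "we obtained the SD (11.0) of the difference in postprandial cognitive test score between the unsaturated fat meal and the saturated fat meal".

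Statistical Analysis names that paired t test first and then adds, for covariate adjustment, a mixed model with a random intercept per participant. This model "will be fit on postprandial test score with the following covariates: study group, preprandial test score at week 0 and 6", followed by further covariates. The preprandial score is named in the singular, with one value per period. The coefficient of study group is taken as the adjusted difference.

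The model for the preprandial score after 7 days of snacks has the same structure, with "study group, preprandial test score at day 0 and 35" plus BMI, age, sex and education. No other analysis of that outcome is stated. Neither model separates a person's stable level from the visit-to-visit deviation. Period appears only in the treatment-by-period interaction used to look for carryover.

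**The concern.** In a two-period crossover the pretest carries two kinds of information: how able the person is in general, and whether that day was better or worse than usual for that person. The first cancels from the walnut-control contrast; only the second can sharpen it. The slope of outcome on pretest is normally much steeper between persons than within persons. One coefficient has to serve both, so it ends up above the within-person slope. The contrast is then over-corrected, and part of the visit noise in the pretest is added to the estimate.

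At stake is the precision of two results: the adjusted version of the primary comparison, and the 1-week cognitive outcome, for which this model is the only stated analysis.

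**Working it through.** **The plan's own figure.** n = (11.0 × (1.960 + 0.842) / 3.5)² = 77.5, rounded up to 78. Power at 78 is 80.2% by the normal approximation and 79.2% by the noncentral t. The stated figure reproduces. The paired standard error is 11.0/√78 = 1.246.

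**Inputs.** From the protocol: n = 78, SD of the difference 11.0, target 3.5. Assumed, because the documents do not give them: score SD 15 (range 12 to 20), equal pretest and outcome variances, a stable level shared by pretest and outcome, and r, the correlation of within-person pretest and outcome deviations. The other covariates are ignored at first.

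**Formulas.**
- Between-period correlation: ρa = 1 − 11.0²/(2 × 15²) = 0.731.
- Same-period pretest-outcome correlation: ρs = ρa + r(1 − ρa).
- Within-person slope: bW = (ρs − ρa)/(1 − ρa) = r.
- Between-person slope: bB = (ρs + ρa)/(1 + ρa).
- Fitted slope b*: with two periods, the random-intercept likelihood works on each person's sum and difference. In large samples b* minimises log Var(sum residual) + log Var(difference residual), that is, log[(1 + ρa)(1 − 2b·bB + b²)] + log[(1 − ρa)(1 − 2b·r + b²)].
- Variance of the walnut effect relative to the paired comparison: planned model 1 − 2b*r + b*²; split model 1 − r²; change score 2(1 − r).

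Example at r = 0.4: b* = 0.83, so 1 − 2(0.83)(0.4) + 0.83² = 1.025. Against the split model this is 1.025/0.84 = 1.220; against the change score it is 1.025/1.2 = 0.854.

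| r | bB | b* | Variance vs split | Variance vs paired | Variance vs change score | Power for 3.5, planned | Power for 3.5, split |
|---|---|---|---|---|---|---|---|
| 0 | 0.845 | 0.70 | 1.490 | 1.490 | 0.745 | 63% | 80% |
| 0.2 | 0.876 | 0.77 | 1.335 | 1.282 | 0.801 | 70% | 82% |
| 0.4 | 0.907 | 0.83 | 1.220 | 1.025 | 0.854 | 79% | 87% |
| 0.6 | 0.938 | 0.89 | 1.130 | 0.723 | 0.904 | 91% | 94% |

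Power is Φ(3.5/SE − 1.960), with SE = 1.246 × the square root of the variance relative to paired. At r = 0, SE = 1.246 × √1.490 = 1.52.

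**Simulation.** REML fits to 1,500 simulated crossovers per setting at n = 78 gave variance ratios of 1.50/1.30/1.18/1.08 against the split model and 1.53/1.26/0.99/0.69 against the period-adjusted paired comparison. Power was 63/70/79/91% against 79/81/86/93% with the split. A separate simulation, set up by correlations, had mean estimates of about 3.5 throughout, so there is no bias. At ρa = ρs = 0.7 it gave a standard error of 1.53 against 1.27 paired, and power of 63% against 79%.

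**Break-even with the paired test.** The planned model loses when b* exceeds 2r. At score SD 15 that is r below about 0.4. At SD 12, b* is 0.709 against 2r = 0.70 when r = 0.35; at SD 20, b* is 0.914 against 0.90 when r = 0.45. The break-even point therefore stays near 0.4.

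**Range over score SD 12 to 20.** The simulated variance ratio against the split model runs from 1.05 to 1.68.

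**Other covariates.** If BMI, age, sex and education explain an assumed 30% of stable between-person variance (score SD 15), the ratio against the split falls from 1.49 to 1.37 at r = 0 and from 1.22 to 1.17 at r = 0.4.

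**The case against.** The strongest reply is that the powered analysis is the paired t test, which this model does not touch. The mixed model follows as an adjustment, is unbiased, and may well improve on the paired test. Fasting and 5-hour tests fall on the same day, while the two meal challenges are 5 weeks apart, so shared day effects could make r sizeable; r = 0 is the unfavourable end of the grid. All of this stands. A reader might infer that the trial is underpowered, or that adjustment must cost power against the paired test. The documents support neither: they give no r and no score SD, and at r = 0.6 the planned model has about 0.7 times the paired variance.

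For the 7-day outcome, the Cognitive Function section describes a difference in change, and the planned model beats a change-score analysis at every r in the table. That also stands, but the split model is more precise than either. In that model, pretest and outcome are a week apart, so no same-day variation is shared. A lower r, and a larger loss, is plausible there but not documented. The SD of 11.0 belongs to the postprandial difference, so the figures are only illustrative for this outcome.

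The coding might also be called detail for an analysis plan that is not shown. If both pretests were entered as two person-level covariates, the walnut effect would neither lose nor gain. But the article writes out the model and its covariates, and the singular preprandial score in a per-period model points to one period-specific covariate. The point concerns a stated model, not an omission.

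**Conclusion.** The point holds as one of efficiency. As written, both cognitive mixed models give an unbiased walnut effect with more variance than necessary whenever the between-person slope exceeds the within-person slope. Under the assumptions above the excess over the split model is about 10% to 50% at score SD 15; the other covariates reduce it without removing it. Against the unadjusted paired comparison the direction depends on r: a loss below about 0.4, a gain above. In large samples the split model is never less precise than the planned model, the paired comparison or the change score, apart from about one degree of freedom.

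The results affected are the adjusted primary estimate and the 7-day cognitive outcome. The primary paired t test, its power and the sample size stand.

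A related wording fault must be settled with it. The postprandial model takes its pretests from weeks 0 and 6, whereas Study Timeline and Meal Challenge put the meal challenges at weeks 0 and 5, and week 6 closes the second intervention. The calculation assumes the pretest of each meal-challenge day.

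**What to change.** In both models, replace the single pretest by two covariates: the participant's mean of the two start-of-period pretests, and each period's deviation from that mean. Include period. An equivalent is to regress the walnut-minus-control outcome difference on the walnut-minus-control pretest difference, with period. State that the pretests are those of the two meal-challenge days, and reconcile the week 0 and 6 label with the visit schedule.

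The cost is a line or two of analysis text and about one degree of freedom. No new data are needed, and the primary test and sample size do not change.

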**Figure 1 figure1:**
[figure not shown]
Study timeline.

At the beginning of each intervention period (weeks 0 and 5), participants reported to the Clinical Research Center on the OSU campus. At the Clinical Research Center, weight, vitals, and waist circumference were measured, sleep and diet questionnaires were answered, fasting indirect calorimetry was completed, a fasting blood draw was collected, and the meal challenge was administered with subsequent blood draws and indirect calorimetry measurements performed hourly for 5 hours. Additionally, cognitive function was measured both fasting and at 5 hours after the meal challenge, and any updates to medications and supplements were recorded. Each intervention period lasted 1 week and concluded with a study visit (week 1 and week 6). At the week 1 and week 6 visits, weight, vitals, and waist circumference were measured. A fasting blood draw was collected, cognitive function was measured, and updates to medications and supplements were obtained. There was a 4-week washout period between intervention periods. Figure 2 describes the measurements and information collected at each study visit. Participants were supplied with enough study snacks to consume 1 study snack per day until their next study visit. No study snacks were consumed during the washout period. At study visits, this study’s team verbally asked participants about adherence to consuming 1 study snack per day, changes to diet or activity, and changes to medications or supplements.

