#### Meal Challenge

At weeks 0 and 5, participants received a high-kilocalorie meal challenge. The meal was approximately 900 kcal with 60 g of fat, 33 g of polyunsaturated fat for the walnut meal and 41 g of saturated fat for the control meal, 60 g of carbohydrates, and 37 g of protein; the meal consisted of a drink and the corresponding intervention period study snack. The macronutrient composition of the meals between the 2 study snacks was equivalent except for the saturated fat, monounsaturated fat, and polyunsaturated fat content. Participants had 20 minutes to consume the entire meal. To measure preprandial and postprandial metabolism, before consuming the meal (fasting) and each hour for 5 hours after consuming the meal, energy expenditure, blood pressure, and heart rate were measured, and venous blood samples and saliva samples were collected.

Energy expenditure was measured using indirect calorimetry (Ultima Series CPX, MGC Diagnostics). For the fasting indirect calorimetry, after arriving for their study visit, participants rested in a quiet, dim room on a hospital bed with the head of the bed at a 30° angle for 30 minutes before assessing energy expenditure over 25 minutes. For postprandial measurements, participants rested for 30 minutes in a hospital bed while being allowed to quietly read, use electronics, or sleep before a 20-minute indirect calorimetry measurement period. A heart rate monitor (FirstbeatTM Bodyguard 3, Firstbeat Technologies) was placed on the participant’s chest and abdomen at the start of the first resting period and measured their heart rate throughout this study’s visit. Fasting and postprandial blood pressure were measured using a blood pressure cuff.

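### The adjusted model of the postprandial score names the week-6 fasting score where the visit schedule gives week 5; run as written, it can bias the adjusted walnut effect

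*Protocol article*

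**What the plan says.** All places are in the protocol article.

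- **Meal challenge.** The Meal Challenge section states: "At weeks 0 and 5, participants received a high-kilocalorie meal challenge". Study Timeline places these visits at the start of each intervention period and adds that "cognitive function was measured both fasting and at 5 hours after the meal challenge". Each postprandial score therefore has a fasting score from the same visit, at week 0 or week 5.
- **End of each period.** Study Timeline puts the closing visits at weeks 1 and 6, after a week of the snack. A fasting cognitive score is taken there, but no meal challenge is given.
- **Adjusted model of the primary outcome.** Statistical Analysis starts with an unadjusted paired t test. It then adds a random-intercept mixed model for the postprandial score with the covariates "study group, preprandial test score at week 0 and 6, BMI, age, sex, education level, and depression score".
- **1-week model, same section.** The model "will be fit on preprandial test score at week 1 and 6 with the following covariates" takes as its baseline the "preprandial test score at day 0 and 35". Day 35 is week 5 (35/7 = 5).
- **Fatty-acid model, same section.** It places the postprandial score at weeks 0 and 5.

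**The concern.** The covariate is meant to be the participant's cognitive level just before the meal. In period 1 the named score (week 0) is that. In period 2 the named score (week 6) is taken one week after the postprandial test it is supposed to precede, and after a week of that period's snack. It is also a response in the 1-week analysis, so one measurement serves as an outcome in one model and as a baseline in another.

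The problem is not that week 6 falls after randomisation. Allocation is made before week 0, so week 5 is post-randomisation too. The problem is that week 6 follows the period-2 outcome and that period's exposure. If a week of walnuts moves the fasting score, the model credits part of the walnut effect to the covariate. Whether it does so is one of the trial's stated secondary questions. The model would therefore perform worst if that secondary hypothesis were true.

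**Working it through.** **1. The plan's own figure.** Inputs from Sample Size: SD of the paired difference 11.0, difference 3.5, two-sided 0.05, power 80%.
n = ((1.960 + 0.842) × 11.0/3.5)² = 77.5, rounded up to 78. Power at 78 is 80.2% by the normal approximation and 79.2% by the noncentral t. The figure reproduces. It rests on the unadjusted paired t test, so no fasting score enters it.

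**2. Direction and size of the shift.** Suppose each row carries one fasting score: week 0 in period 1, week 6 in period 2. Let δ be the 1-week walnut effect on the fasting score and β the covariate slope. Only participants who eat walnuts second have their week-6 score raised by δ, and they supply half of the walnut rows. The mean covariate of walnut rows then exceeds that of control rows by δ/2, so

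adjusted estimate ≈ true effect − β × δ/2.

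**3. Simulation of the 2×2 crossover.** From the document: n = 78, true effect 3.5, SD of the paired difference 11.0. Assumed, because the document does not give them: the variance shares and δ. There were 500 trials per scenario, with a Monte Carlo error of about 0.06 to 0.07.

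| Between-subject share | Same-day share of within-subject variance | β (at δ = 3.5) | Estimate, δ = 0 | Estimate, δ = 3.5 | Formula, δ = 3.5 | Estimate, δ = 7 |
|---|---|---|---|---|---|---|
| 0.5 | 0 | 0.43 | 3.55 | 2.71 | 2.75 | 2.07 |
| 0.5 | 0.3 | 0.53 | 3.46 | 2.57 | 2.57 | 1.77 |
| 0.8 | 0 | 0.77 | 3.46 | 2.25 | 2.15 | 0.94 |
| 0.8 | 0.3 | 0.81 | 3.50 | 2.14 | 2.08 | 0.76 |

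With the week-0/week-5 score the estimate averages 3.47 to 3.56 in every scenario. A 4-point practice shift at week 6 with δ = 0 gives 3.49, so a shift common to both sequences does no harm.

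**4. The other reading.** If the week-0 and week-6 scores both enter every row as participant-level covariates, the simulated estimate equals the mean paired difference exactly, so there is no bias. With the full covariate list, that equality also needs the other covariates to be constant within a participant.

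**5. Precision.** Either reading leaves out the period-2 same-visit fasting score. The cost depends on how much fasting and postprandial scores share on the day. In the row-matched model at δ = 0, the SD of the estimate goes from 1.30 (week 5) to 1.48 (week 6) in the 0.8/0.3 scenario, from 1.24 to 1.26 in the 0.5/0.3 scenario, and shows no consistent change where no same-day share is assumed. Under the participant-level reading the estimate keeps the precision of the paired difference and gains nothing from the fasting scores.

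**6. Carryover test.** The plan tests carryover by a treatment-by-period interaction in the mixed models. A row-matched week-6 covariate distorts period 2 only, which imitates an interaction. In 3,000 simulated trials per scenario without true carryover (assumed 60% between-subject and 15% same-day variance), the share flagged rose from 5% to 11% at δ = 3.5 and to 31% at δ = 7. The participant-level reading does not protect this test, because the interaction is a contrast between sequences and the week-6 score differs by sequence when δ is not zero.

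**The case against.** The strongest reply is that this is a typing error. The same section uses day 35 and week 5 elsewhere, nothing in the article argues for adjusting on week 6, and a competent analyst would probably use week 5. That is likely right. It does not remove the point, because the published text states a definite rule. An analyst who follows it fits the wrong model, and one who quietly departs from it leaves a deviation to be explained.

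Three further objections limit the claim, and all stand:

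- A reader might infer that the adjusted walnut effect is biased outright. The document does not support this. Bias needs a non-zero 1-week effect and a row-matched covariate, and the document establishes neither. It pulls the estimate down only if both effects favour walnuts; with opposite signs it would push the estimate up.
- A reader might infer that the primary comparison as a whole is compromised. The first-named comparison is the unadjusted paired t test, which uses no fasting score, and the mixed model is described as a further adjustment. If carryover is declared, the fallback uses period 1 only, where week 0 is the right baseline.
- The sizes depend on assumed variance shares and assumed values of δ. Nothing in the document suggests that the 1-week effect is as large as the 3.5-point acute difference.

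The protection of the paired t test has one gap. A significant interaction leads to discarding period 2 and replacing the paired test with a two-sample test. If the carryover term is fitted in the model with the week-6 covariate, the error can reach the primary conclusion by that route.

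**Conclusion.** The point holds as an error in a stated analysis rule with conditional consequences. It is certain from the text that the named week does not match the meal-challenge visits or the other models in the section. That it is a slip for week 5 is an inference, though a strong one.

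Run literally with one score per row, the adjusted effect moves by about −β × δ/2. In the illustrative case of a true effect of 3.5 and δ = 3.5, the estimate is about 2.1 to 2.7, a loss of roughly 23% to 39% ((3.5 − 2.71)/3.5 to (3.5 − 2.14)/3.5). At δ = 0 there is no bias. If both scores enter every row, the treatment estimate is not biased for any δ, but the carryover term can still be disturbed when δ is not zero. The paired t test and the sample size of 78 stand. A claim that the trial's primary result is biased would go beyond the document. The correction is still needed, because this is the only adjusted model given for comparing the snacks on the primary outcome.

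**What to change.** In Statistical Analysis, replace the week-0-and-6 covariate of the postprandial model with the fasting score taken at the same meal-challenge visit: week 0 for period 1 and week 5 for period 2, one value per row. Add a sentence that no week-1 or week-6 score enters this model, including when the treatment-by-period term is fitted. Record the correction before the data are analysed, so that it reads as a correction and not as a choice made after seeing results.

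The cost is one phrase and one sentence. The week-5 fasting score is already collected, and the sample size does not change.

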## Methods

### Study Design and Setting

The EFFECT study was a 7-week randomized single-blinded placebo-controlled crossover design study. This study consisted of a 1-week run-in period followed by two 1-week intervention periods separated by a 4-week washout period. All participants were asked to consume 1 study snack per day throughout this study, except during the washout period. After completing the run-in period, participants were randomly assigned to the order of snack consumption: control snack followed by walnut snack or walnut snack followed by control snack. All study visits took place at The Ohio State University (OSU).

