### Strengths and Limitations

The EFFECT study uses a randomized, crossover design with a 4-week washout period between interventions. Thus, a strength of this design is that participants served as their own controls. A total of 4 weeks should be sufficient to prevent any carryover effects from the first intervention. Using a run-in period could be considered a limitation, as a study snack used to acclimate participants to consuming 1 study snack per day would be a deviation from their usual diet. However, the fat profile of the run-in period snack is comparable to the typical American diet. An inherent limitation to studying SCI is the subjective nature of the cognitive impairment, as reliance on a self-report of cognitive issues is necessary. Similarly, adherence to the interventions is partially reliant on self-reported consumption. However, changes in fatty acid profiles in erythrocytes were also used as a measure of adherence.

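### The carryover pretest that can discard period 2 does not identify carryover, and it lifts the type I error above the stated 0.05

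*Protocol article*

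**What the plan says.** Under Study Design and Setting the trial is a two-sequence, two-period crossover: "This study consisted of a 1-week run-in period followed by two 1-week intervention periods separated by a 4-week washout period". Under Statistical Analysis the main comparison is the paired one: "Postprandial cognitive test scores will be compared between the control and walnut group using a 2-sided paired" t test. A mixed model with covariates, including the preprandial score, follows. Carryover is then to be judged by adding a treatment-by-period interaction to the mixed models, with this consequence: "Significant interaction indicates the existence of a carryover effect, in which case we will only use data from the first treatment period". The period 1 data would be analysed by a two-sample t test and linear regression. No significance level is given for the interaction test.

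Under Sample Size the trial is sized for the paired test alone: "We had 80% power with 78 participants to detect a difference of 3.5 in postprandial cognitive test score", with an SD of the within-person difference of 11.0 and a two-sided test "with a type I error of 0.05". No between-person SD, within-person correlation or power for a period 1 comparison is given.

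Under Strengths and Limitations the washout is defended: "A total of 4 weeks should be sufficient to prevent any carryover effects from the first intervention".

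**The concern.** This is the two-stage crossover procedure, and it has two faults here.

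First, the inference from the trigger is wrong. With two sequences and two periods, the treatment-by-period contrast is the same contrast as the difference between sequence groups. Unequal carryover, chance imbalance between the groups and a treatment effect that differs by period all feed into it, and the data cannot tell them apart.

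Second, the trigger and the fallback share data. If the group that had walnuts first happens to score higher, the interaction test and the period 1 comparison are both pushed away from zero. The period 1 test is therefore used mainly in trials where it is already likely to reject. The nominal 0.05 no longer holds for the procedure as a whole, and the plan makes no adjustment for this.

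At stake are the error rate of the primary comparison and, whenever the rule fires, the within-person comparison that the protocol names as a strength.

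**Working it through.** **Inputs from the protocol article.** N = 78, difference 3.5, SD of the within-person difference 11.0, two-sided 0.05 (Sample Size). Two sequences in blocks of 2 and 4 (Randomization), so about 39 per sequence.

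**Assumptions.** Pretest at 0.05, with 0.10 also tried. Within-person correlation ρ of the postprandial score between 0.3 and 0.9. Simulations for type I error have no treatment, period or carryover effect.

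**1. The plan's own figure.** Normal approximation: (11 × (1.960 + 0.842) / 3.5)² = 77.6, so 78. With the noncentral t, 3.5 / (11/√78) = 2.81 on 77 df gives 79.2% power. The stated 80% is reproduced.

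**2. Link between pretest and fallback.** Single-score SD = 11 / √(2(1 − ρ)). The unadjusted pretest compares subject sums between sequences; the fallback compares period 1 scores. Their correlation is √((1 + ρ)/2), which is 0.81 at ρ = 0.3, 0.92 at 0.7 and 0.97 at 0.9.

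**3. Type I error, unadjusted pretest at 0.05.** The paired test uses within-person differences and is essentially independent of the sums. Overall error is therefore about 0.95 × 0.05 + 0.05 × c, where c is the simulated false rejection rate of the period 1 test once the pretest is significant (400,000 trials per setting).

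| ρ | SD | c | Formula | Simulated overall | Period 1 power, 39 v 39 |
|---|---|---|---|---|---|
| 0.3 | 9.3 | 0.442 | 0.070 | 0.070 | 37.5% |
| 0.5 | 11.0 | 0.529 | 0.074 | 0.074 | 28.4% |
| 0.7 | 14.2 | 0.632 | 0.079 | 0.080 | 18.9% |
| 0.8 | 17.4 | 0.699 | 0.082 | 0.082 | 14.2% |
| 0.9 | 24.6 | 0.786 | 0.087 | 0.087 | 9.5% |

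With the pretest at 0.10, overall error is 7.7% to 9.4%. The paired test alone gives 5.0%.

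**4. Type I error, pretest adjusted for the preprandial score.** At ρ = 0.5, 0.7 and 0.8 (200,000 trials each), overall error is 6.2%, 5.7% and 5.5% if the fallback is the unadjusted t test, and 6.6%, 6.6% and 6.5% if it is the adjusted regression. With the t test fallback the excess shrinks as ρ rises.

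**5. Power of the fallback.** Unadjusted standard error = SD × √(2/39). At ρ = 0.7 this is 14.2 × 0.226 = 3.22, so 3.5 / 3.22 = 1.09 and power is 18.9%. The last column of the table gives the range. Period 1 regression adjusted for the preprandial score has 31% to 35% (ρ from 0.8 to 0.5).

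**6. Overall power without carryover.** The rule fires in about 5% of trials. Overall power is about 78% with the unadjusted pretest and 77% to 78% with the adjusted one, against 79% for the paired test.

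**7. Sensitivity to real carryover.** Suppose a carryover of 3.5 points in one sequence. At ρ = 0.7 the SD of the sum is 14.2 × √3.4 = 26.2 and the standard error is 26.2 × 0.226 = 5.93. The ratio is 0.59 and detection is about 9%. If the pretest is adjusted for preprandial scores that are themselves free of carryover, their sum correlates 2ρ/(1 + ρ) = 0.82 with the postprandial sum. The standard error becomes 5.93 × √(1 − 0.82²) ≈ 3.4, and detection is about 18%.

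**The case against.** The best defence is that the pretest sits in the mixed models, which carry the preprandial score. Adjustment removes much of the between-person variation that drives the inflation, so the fairer figure may be 5.5% to 7%. That stands, and it is why both ranges are given. It reduces the excess but does not remove it, and it leaves the aliasing untouched. The rule is also prespecified, so this is not an improvised change of analysis. Prespecification does not restore the error rate.

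A reader might infer four stronger points that the document does not support:

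- **The trial has about 19% power.** That figure needs a within-person correlation near 0.7, which is not given. It concerns only the unadjusted t test and only trials in which the rule fires.
- **The crossover as a whole loses its power.** Without carryover the loss is one to two percentage points.
- **An ordinary practice gain would be read as carryover.** This requires the interaction to be fitted without a period main effect. The covariate list names none, but a condensed article need not spell out main effects, and the Cognitive Function section claims minimal practice effects.
- **The run-in before period 1 and the snack-free weeks before period 2 create an interaction.** Both sequences share that history, so it produces a period effect. An interaction would need the history to alter the walnut-control difference, and nothing in the document shows that.

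**Conclusion.** The rule is wrong as written. A significant interaction does not establish carryover in this design, and letting it replace the primary analysis gives an overall type I error of about 5.5% to 9%, not 5%. The upper part of that range (7% to 9%) belongs to an unadjusted pretest with ρ from 0.3 to 0.9. The lower part (5.5% to 7%) belongs to a pretest adjusted for the preprandial score, run at ρ from 0.5 to 0.8. Both assume a 0.05 pretest, equal sequences and no carryover.

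The power problem is conditional. When the rule fires, about 39 versus 39 remain, with power of about 10% to 38% unadjusted or 31% to 35% with baseline adjustment, for a trial planned at 80%. In return the rule offers little protection, since a carryover as large as the target effect would usually go undetected. It also sits awkwardly with the protocol's own view that the washout is long enough.

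**What to change.** Delete the sentence that restricts the analysis to period 1 after a significant interaction. State that the both-period analysis with a period main effect is the only primary analysis whatever the interaction shows, and rest the absence of carryover on the 4-week washout. Report the interaction estimate with its confidence interval, and the period 1 result, as sensitivity results that never replace the primary.

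If the preprandial score stays as a covariate, first reconcile its timing. Statistical Analysis names weeks 0 and 6 for the postprandial model, whereas Study Timeline places the meal challenges, with fasting cognitive testing, at weeks 0 and 5.

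The cost is wording only, settled before outcome data are analysed. A period term uses one degree of freedom (76 instead of 77). The real downside is that no automatic fallback remains if a large carryover did occur, but the pretest would rarely have found one.
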